### Outcome and Process Evaluation

#### Target Population

A cross-sectional audit will be conducted at baseline, 6 months, and 13 months after the start of the implementation phase. During each cross-sectional audit, a random sample of hospitalized patients will be approached to participate during one day from 8 AM to 8 PM. Eligible patients are 18 years or older, have sufficient Dutch or English speaking ability and reading skills, and are admitted for at least 24 hours. The following exclusion criteria will be used: inability to perform independent transfers prior to hospital admission, delirium, obligatory bed rest as indicated by the attending physician, expectation to be discharged before 12 AM on the day of observation, and receiving end-of-life care. Random selection of potential participants will be performed using a computer-generated list based on the room numbers of the hospital ward, and potential participants will be approached one or two days prior to the day of observation. In the case of refusal or when the patient does not meet the study criteria, the investigator will approach the patient in the next hospital room on the computer-generated list. Each participant can only be enrolled once. No a priori sample size calculations are performed. Resources allow us to spend 1 year at the iterative (cyclical) process at each hospital ward; therefore, we determined a pragmatic sample size. Considering the duration of the different steps, including three cross-sectional audits, the inclusion of 65 participants is deemed feasible at each hospital ward. Given this sample size (n=110 at baseline and n=110 at 13 months) and assuming normality of the outcome parameter, we will be able to detect an effect size of 0.38 or higher for the primary outcome (two groups *t* test of equal means; α=.05; 1−β=.80; nQuery 8, Statistical Solutions Ltd).

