#### Primary Outcome

The primary outcome is the total amount of physical activity in minutes (>1.4 metabolic equivalent tasks [METs] [33]), which will be measured during each cross-sectional audit from 8 AM to 8 PM using the PAM AM400 wireless accelerometer. The PAM AM400 is a 2-cm-wide coin and is waterproof, and it will be attached to the ankle. The PAM AM400 measures accelerations 10 times per second in three dimensions and converts these accelerations to the total amount of time of physical activity in minutes >1.4 METs. METs is a concept that is used to assign an intensity value to specific activities. In healthy participants, light-intensity physical activity involves <3.0 METs, moderate physical activity involves 3.0-6.0 METs, and vigorous physical activity involves >6.0 METs [33]. Sedentary behavior is defined as ≤1.5 METs [34]. In addition to the total amount of physical activity in minutes >1.4 METs, the PAM AM400 compares each second of physical activity with the following three predefined intensity zones: light physical activity (1.4-3.0 METs), moderate physical activity (3.0-7.0 METs), and vigorous physical activity (>7.0 METs), and measures the derivative of METs for 24-h physical activity (PAM score = [METs − 1] × 100 averaged over the day). The validity and reliability of the PAM in healthy adults is moderate to good for assessing the estimate of energy expenditure [24,25].

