### Data Analysis

All analyses will be conducted using IBM SPSS Statistics version 25 (IBM Corp). Patients’ characteristics in each cross-sectional audit will be described using descriptive statistics. Primary outcome evaluation will be performed between month 0 and month 13 across all hospital wards, and only the data of patients wearing the PAM during the entire observation period (8 AM-8 PM) will be used. The total amount of physical activity in minutes will be tested on normality with the Kolmogorov-Smirnov test and will be visually inspected using Q-Q plots. A logarithmic transformation will be considered in case of nonnormality. Analysis of covariance will be used to assess the difference in the total number of minutes of physical activity (>1.4 METs), whereby the covariates include independence in mobility and the presence of a urinary catheter. Both covariates are based on unpublished results of multivariable regression models considering various patient factors in relation to physical activity. In case nonnormality persists after logarithmic transformation, a Poisson regression model will be considered using the same covariates.

Additionally, data of behavioral mapping observations will be categorized into different activity types, from which time spent lying in bed between 8 AM and 8 PM in percentage will be derived. The difference in time patients spend lying in bed will be assessed among months 0, 6, and 13. An interrupted time series (ITS) will be used to evaluate the changes in length of stay and discharge destination among the following three predefined periods: 12 months prior to the implementation phase, 12 months implementation phase, and 6 months after finishing the implementation phase [38].

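### The Poisson fallback for the primary outcome makes no stated allowance for overdispersion, so its standard errors would very likely be too small whenever that branch is used

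*Protocol article*

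**What the plan says.** The outcome is defined under Primary Outcome: "The primary outcome is the total amount of physical activity in minutes", counted above 1.4 METs between 8 AM and 8 PM, so it can lie anywhere from 0 to 720.

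The Data Analysis section then sets out a sequence:

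1. "The total amount of physical activity in minutes will be tested on normality with the Kolmogorov-Smirnov test and will be visually inspected using Q-Q plots".
2. "A logarithmic transformation will be considered in case of nonnormality".
3. ANCOVA compares month 0 with month 13, adjusting for independence in mobility and urinary catheter.
4. "In case nonnormality persists after logarithmic transformation, a Poisson regression model will be considered using the same covariates".

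Nothing is said about how the variance is estimated in step 4. The precision statement under Target Population covers only the normal-theory route: "Given this sample size (n=110 at baseline and n=110 at 13 months) and assuming normality of the outcome parameter", followed by "we will be able to detect an effect size of 0.38 or higher for the primary outcome".

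**The concern.** A Poisson model suits counts of independent events, where variance equals mean. Active minutes are a total duration that differs between patients for many reasons. The study pools five wards, from surgery to cardiology, and adjusts for only two patient factors. The spread between patients will therefore very likely be much wider than a Poisson model allows. Its model-based standard errors are then too small by the square root of the variance-to-mean ratio, p-values are too small, and confidence intervals are too short.

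The gate adds to the problem. Normality is examined on the raw minutes, whereas ANCOVA's assumption concerns the residuals. A skewed or ward-mixed outcome can thus move the analysis away from a method that holds its error rate and towards one that does not. Neither the Kolmogorov-Smirnov test nor a Q-Q plot checks dispersion, so nothing in the sequence would warn the analyst. At stake are the p-value and interval for the primary outcome.

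**Working it through.** **The plan's own figure.** With 110 per group, two-sided alpha 0.05 (the article does not state sidedness) and power 0.80, n per group for an effect of 0.38 SD is 2 × (1.960 + 0.842)² / 0.38² = 108.7, or 109. Exact t-test power with 110 per group is 0.801. The stated 0.38 reproduces and is not in question, but it assumes normality and does not cover the Poisson step.

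**Is variance = mean plausible?** The article gives no mean, so take 60 minutes as an assumption. A Poisson outcome would have SD √60 = 7.7 minutes, and the detectable 0.38 SD would be 0.38 × 7.7 = 2.9 minutes. So small a spread between patients in a 12-hour window, across five wards, is hard to believe.

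**Dependence on the unit.** The Primary Outcome section says the device classifies each second, so minutes are a reporting choice. With phi = variance/mean, assumed mean 60 and SD 30 minutes give phi = 900/60 = 15. The same data give phi = 900 in seconds and 0.25 in hours. By the formula below, the error of an unscaled Poisson test is then 61%, 95% and below 0.01%. A null simulation (gamma minutes, 1,000 runs) gave 58%, 94% and 0%, against 5% for a linear model and for Poisson with robust variance.

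**Error of the Poisson step.** If the true residual variance is phi times the mean, an unscaled Poisson standard error is too small by √phi, and

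type I error = 2 × [1 − Φ(1.96/√phi)].

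| phi | SE too small by | SD this implies at mean 60 | Type I error |
|---|---|---|---|
| 2 | 1.4 | 11 | 17% |
| 5 | 2.2 | 17 | 38% |
| 10 | 3.2 | 24 | 54% |
| 26 | 5.1 | 39 | 70% |

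**Error of the whole sequence.** This was simulated with no true effect: 110 versus 110, two prognostic covariates, 600 runs per scenario, assumed means 30-100 minutes and coefficients of variation 0.5-0.9. The rule was made automatic: Kolmogorov-Smirnov at 5% on minutes, then on log(minutes + 1), then unscaled Poisson. With the Lilliefors correction:

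| Assumed shape | Runs reaching Poisson | Type I error |
|---|---|---|
| Lognormal | 4-15% | 8-15% |
| Gamma | 22-78% | 18-64% |
| Ward mixture | 25-53% in the four settings listed | 20-42% |
| Weibull | 86-89% in the two settings at mean 100 | 43-71% |
| 15% near-immobile | about 100% | 65-80% |

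With an uncorrected Kolmogorov-Smirnov test, the gamma, lognormal and ward-mixture cases fall to 4-9%, because Poisson is rarely reached. The near-immobile case stays at 38-80%. With 600 runs, simulation error is about ±2 points near 5% and ±4 near 70%.

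**With the variance handled.** In the same scenarios, the Poisson step has an error of about 3-8% with a Pearson scale and 4-8% with robust variance. The whole sequence with a scaled Poisson step gives 4-8%. ANCOVA on untransformed minutes gives 3-6%.

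**The case against.** The strongest reply is that the article underspecifies rather than errs. It names a Poisson model without ruling out a scale parameter or robust variance, both of which its chosen software offers, and such detail often sits in an analysis plan that is not shown. That the model would be unscaled is an inference. ANCOVA is the main method; the log and Poisson steps are only to be considered, and Q-Q plots bring in judgement that an automatic rule does not mimic. All this is correct and lowers the weight of the point. It does not remove it: the article itself chose this model for the primary outcome, and applying it in its standard form gives wrong standard errors. Leaving the step optional also postpones the choice until the data are seen.

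A reader might go further and infer that the sequence would declare an effect by chance in about 70% of null studies. The documents do not support that. They give no mean, SD or distribution of minutes, and they do not say which version of the Kolmogorov-Smirnov test applies. A figure near 70% needs a ratio near 26 in the Poisson step, or a distribution that sends nearly every study there, for instance one with a cluster of patients at or near zero. Nothing in the article points to such a cluster. Patients on obligatory bed rest and those unable to transfer independently before admission are excluded, and only full-day wearers are analysed. Assumed ranges such as mean 20-90 and SD 15-45 minutes do not settle the matter either: taken freely, they allow ratios from 15²/90 = 2.5 to 45²/20 = 101.

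**Conclusion.** The point holds for the Poisson branch. Used as named, without correction, it would very likely understate the standard error of the primary comparison. The tabulated 17% to 70% depends only on the variance-to-mean ratio, which the documents do not give; that the ratio is well above 1 is a judgement from the nature of the outcome and the mix of wards. For the sequence as a whole no single figure can be defended. The range is about 4-15% if minutes are near-lognormal, up to about 80% if nearly every study reaches the last step, and it depends on the assumed distribution, the test version and an automatic rule. Since the step is conditional and the first-line ANCOVA holds its error rate in these scenarios, the point should be corrected but does not by itself undermine the primary analysis.

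**What to change.** In the Data Analysis section, do one of the following:

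- Replace the fallback with a log-link model that allows overdispersion: Poisson with a Pearson scale or robust standard errors, or negative binomial.
- Keep ANCOVA on minutes throughout, with robust or bootstrap confidence intervals, and drop the fallback.

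In either case, judge normality on the residuals of the fitted model rather than on the raw minutes. The cost is one or two sentences and a different option in the same software. The p-value will be less favourable than under unscaled Poisson.

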## Results

This study is ongoing. The first participant was enrolled in January 2018 at the gastrointestinal and oncology surgery ward. The last outcome evaluation and process evaluation are planned for May and June 2020, respectively. Results are expected in April 2021. A summary of all participation types within this study can be found in Multimedia Appendix 1.

## Discussion

While the amount of evidence on the negative consequences of physical inactivity during hospitalization continues to grow, few studies have evaluated the effectiveness of interventions that have been specifically tailored (ie, developed and implemented) in collaboration with the target population. So far, several studies revealed that increasing physical activity in general or encouraging early mobilization (after admission or operation) has a positive influence on physical functioning in daily activities, the duration of admission, and discharge home [11,13]. However, these studies often focus on unilateral interventions and have been performed in a specific context, while physical inactivity seems to affect patients in all hospital wards and patients of all ages [27]. The integration of multiple interventions in daily hospital care entails various challenges, as also described in the quality improvement projects of Mudge et al and Hoyer et al [9,16]. The Eat Walk Engage program of Mudge et al describes an approach using multiple interventions, which demonstrated a reduced length of stay after implementation in older hospitalized patients [9]. In addition, the currently ongoing Hospital in Motion study of van Delft et al describes the usage of multiple interventions tailored to tackle the numerous described barriers perceived by health care professionals and hospitalized patients [29]. The Better By Moving study will contribute to this research by providing more insight into the effectiveness of interventions that are developed bottom-up and in cocreation with the target population and by thoroughly analyzing the process of cocreation.

The strength of the Better By Moving study is the thorough problem analysis of actual performance, and barriers and enablers, which will be carried out prior to the development of the first intervention. More specifically, the barriers and enablers perceived by patients or health care professionals will be assessed through different mixed methods, such as surveys, physical measurements, observations, interviews, and focus groups. In addition, we hypothesize that the extensive analysis will create support among health care professionals, manifest ownership among local stakeholders, and facilitate the development of a local testing and implementation plan. Second, colearning in the development and implementation of new interventions together with local stakeholders from five different hospital wards can offer both an in-depth and a broad perspective on what works and what does not work when trying to improve physical activity in hospitalized patients. Third, the use of evidence-based behavioral change theories, such as the TDF [31] and BCW [32], makes it more likely that the underlying reasons for physical inactivity in hospitalized patients will be identified and countered [31,32]. Finally, the ITS analysis, which will be used, is considered one of the strongest quasiexperimental designs to evaluate outcomes such as length of stay and discharge destination. So far, none of the previously published studies investigating physical activity–improving interventions incorporated ITS analysis.

Diverse factors could challenge the success of the Better By Moving study. First, several “system” factors may affect the implementation process, such as a change in the environmental context (ie, staff turnover, competing trials, and workload) and the hospital ward culture (ie, attitude to change, commitment, and motivation) [40]. For instance, the planned renovation of the participating hospital wards and the recent merger with the Vrije Universiteit Medical Center may create a lack of focus and provide additional workload. Second, because it is not known in advance which interventions will be developed and implemented, the achieved effect may differ in each hospital ward owing to differences in the interventions used. To counter this as much as possible, we will provide for both an overall and a ward-specific analysis. Third, changing the health care professionals’ and patients’ behaviors toward in-hospital physical activity through the development and implementation of multiple interventions in cocreation takes time. While we have 12 months for each hospital ward to cocreate interventions, important changes in hospital culture, environmental context, and outcomes may arise after the last cross-sectional audit. Lastly, a pre-post mixed-methods design is used to investigate if interventions developed and implemented in cocreation improve physical activity among patients. To evaluate the effect of an intervention, a randomized controlled trial is considered the gold standard. With respect to cocreational bottom-up intervention development and implementation, in which the process, to a large extent, determines the outcome, it is considered not feasible to use a control group. Instead, we aim to evaluate the impact of our interventions on physical activity as representative as possible by approaching a random sample of at least 110 hospital patients using a computer-generated list based on hospital room numbers before and after the implementation of interventions.

By using cocreation to develop and implement interventions and by performing a process evaluation, useful insights will be provided on the effect and underlying processes of bottom-up intervention development and implementation in close collaboration with the target population and local stakeholders. Using this information, health care professionals, managers, and researchers will be able to better assess the elements that do and do not work with regard to improving physical activity in daily hospital care.

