## Methods

### Study Design

An uncontrolled pre-post embedded mixed-methods study is designed to evaluate whether we can improve physical activity in hospitalized patients by using interventions that we develop and implement in cocreation. The development and implementation describe the iterative (cyclical) process of planning, conducting, reflecting, and refining, which is being used in close collaboration with local stakeholders, such as patients, health care professionals, and managers [19]. The study has been approved by the Medical Research Ethics Committee of the Amsterdam University Medical Centers (Amsterdam UMC), Academic Medical Center (W17_479 #18.003 and W19_213 #19.258). Written informed consent will be obtained from all participants in both the outcome and process evaluations.

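### The interrupted time series for length of stay and discharge destination has no comparison series, although the protocol itself names a merger and ward renovations that could fall inside it

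*Protocol article*

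**What the plan says.** Under Study Design the protocol is open about its type: "An uncontrolled pre-post embedded mixed-methods study is designed to evaluate". Under Data Analysis, "An interrupted time series (ITS) will be used to evaluate the changes in length of stay and discharge destination", over three periods: "12 months prior to the implementation phase, 12 months implementation phase, and 6 months after finishing the implementation phase". It names no comparison series and no term for other events. Under Secondary Outcomes, both outcomes come from hospital administrative data. The Abstract and the Discussion promise results overall and ward by ward.

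For both of these outcomes, the Discussion says that "the ITS analysis, which will be used, is considered one of the strongest quasiexperimental designs to evaluate outcomes such as length of stay". It then lists system factors that "may affect the implementation process, such as a change in the environmental context", and gives as its example that "the planned renovation of the participating hospital wards and the recent merger with the Vrije Universiteit Medical Center may create a lack of focus", besides adding workload. On controls it says that, for bottom-up cocreation, "it is considered not feasible to use a control group", and moves directly to the random sample of patients for the activity outcome.

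**The concern.** An ITS guards against a stable underlying trend. It does not guard against a second event in the same window. A merger or a ward renovation can plausibly change bed allocation, case mix or discharge routes, and so move length of stay and discharge home directly. The protocol discusses both events as obstacles to implementation, and nothing in the stated analysis separates them from the programme. Treating them as possible confounders is an inference, but a modest one.

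The reason given for having no control concerns cocreation and the activity sample. A comparison series of routinely recorded stays needs no patient contact and no cocreation, so that reason does not exclude one. At stake is how firmly two of the three secondary aims can be attributed to the programme.

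**Working it through.** **Inputs from the protocol.** Periods of 12, 12 and 6 months (Data Analysis). Five wards of 29 beds in a 1000-bed hospital (Setting), so 5 × 29 = 145 study beds and about 855 others. Wards start one after another (Steps 1 and 5). First enrolment was in January 2018 and the last outcome audit is planned for May 2020 (Results). That is 28 months; with the last audit 13 months after a ward's start, the last start is near month 28 − 13 = 15.

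**Assumptions.** Monthly points; ward starts at calendar months 0, 4, 8, 12 and 15; event dates and sizes, which the documents do not give.

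**The plan's own figure.** The only power figure, a detectable effect of 0.38 with 110 against 110, reproduces (0.379 by the exact two-sided t test). It concerns physical activity and has no bearing here.

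**One ward.** Model: y = b0 + b1·t + b2·A + b3·A(t − 12) + b4·B + b5·B(t − 24), where A and B switch on at months 12 and 24. The programme effect is set to 0, a 1-unit outside shift is added, and least squares is fitted:

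| Outside shift | False level change at start | False mean effect, implementation | False mean effect, afterwards |
|---|---|---|---|
| Before the series begins | 0 | 0 | 0 |
| Permanent, 6 months before start | −0.32 | −1.01 | −2.14 |
| Permanent, at start | 1.00 | 1.00 | 1.00 |
| Permanent, 6 months after start | −0.19 | 0.50 | 1.00 |
| Six months long, ending at start | −1.32 | −2.01 | −3.14 |
| Six months long, from start | 1.19 | 0.50 | 0.00 |

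Timing alone decides the size and sign of the error.

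**Five wards pooled on their own clocks.** For a common permanent shift at calendar month −6, 0, 4, 8 or 12, the average false level change is −0.12, 0.11, 0.09, 0.07 or 0.18. False mean effects run from −0.34 to 0.32 during implementation and from −0.69 to 0.55 afterwards. The stagger helps but does not remove the problem.

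**With a comparison.** If comparison wards share a fraction s of the shift, the difference series keeps (1 − s) × shift: 0 at s = 1, 0.50 at s = 0.5, and 1.00 at s = 0. Renovation confined to study wards is the case s = 0.

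For the five wards alone, take ward intercepts, calendar-month effects and common programme terms over 12 + 15 + 18 = 45 calendar months. A shift common to all wards is then absorbed exactly. The standard error of the level change is 0.332 residual SDs, against 0.311 with a linear trend instead of month effects (0.332/0.311 = 1.07).

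**False positives, length of stay only.** Assume 120 admissions per ward per month, mean 6 days and SD 6, so a monthly mean has standard error 6/√120 = 0.55 day. Assume also one hospital-wide step at a random month of the roll-out and a joint 4-df test of the programme terms. Over 3000 runs per setting the pooled rates are 4.9%, 6.7%, 10.2% and 18.7% for steps of 0, 0.3, 0.5 and 0.8 day. Subtracting a control series that shares the step fully gives 4.1 to 4.8% throughout. For a single ward with the step at its start, the rate is about 13 to 14% at 0.5 day and 29% at 0.8 day.

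**The case against.** The strongest reply is that nothing shows either event to bias anything. The merger is called recent and the renovation planned, without dates, and a shift before a ward's series begins causes no bias. This stands: the bias is conditional, and the missing dates are a reason to record them.

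The false-positive rates rest wholly on assumed inputs, the return to about 4 to 5% is built in by assuming a fully shared step, and discharge destination was not simulated. This stands too, so those figures are illustrations only.

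The design is declared uncontrolled, sequential starts give partial protection, and the process evaluation counts context acting on outcomes as within its scope. All true. But interviews do not adjust an estimate, and stagger does nothing within one ward's series.

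Model terms are commonly left to an analysis plan that is not shown. That covers the detail, but not the design, which is fixed as uncontrolled, or the strength claimed for it.

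A reader might infer that comparison series already exist in the same extract. The documents do not say so: the description of the administrative data can mean the five study wards only, and the 1000-bed figure makes outside wards plausible, not certain. A reader might also expect control wards to remove both events. They do not remove a renovation confined to study wards.

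**Conclusion.** The concern holds in conditional form. The ITS has no comparison series, the protocol names two events that could disturb it, and the argument against a control group does not reach routine data. If an event falls inside a ward's window and moves these outcomes, the false effect can range from nothing to about twice the size of a permanent shift (about three times for a six-month one), in either direction. The exposure is greatest in the ward-specific analyses.

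A reader might infer that the two secondary aims cannot be answered. The documents do not support that: without dates or sizes, the most that can be said is that effects cannot be securely attributed to the programme. The general statement that "considered one of the strongest quasiexperimental designs to evaluate outcomes such as length of stay and discharge destination" is too strong for a series with named possible co-events and no comparison. The point affects secondary outcomes only. It should be acted on because the remedy is cheap.

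**What to change.** 1. Extract length of stay and discharge destination for all five wards over the same calendar months and analyse them jointly in calendar time, so that wards not yet started are concurrent controls.
2. Where comparable non-participating wards can be extracted from the administrative data, add them as a comparison series and report the difference in level and slope change, overall and per ward. They matter most for the later months: under the assumed starts, an untouched study ward remains for only three months of the first ward's post-implementation period (months 12 to 14).
3. Record the merger date and each ward's renovation dates. Enter renovation as a ward-specific time-varying term, because a control series removes only what the control wards share.
4. Qualify the Discussion's claim for the ITS, so that changes in these two outcomes are not presented as securely due to the programme without this comparison.

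The cost is a wider administrative extract, a log of dates, a few model terms and a small loss of precision (about 7% on the standard error in the five-ward illustration). The joint model also assumes that wards share calendar effects and have similar programme effects, which the protocol itself doubts, so ward-specific differences should still be shown. Control wards may have been exposed to the hospital-wide presentations and workshops of Step 1, which would dilute the estimate by an unknown amount.
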